# Study Assessments:

Participants will have a minimum of two follow-ups. Clinical assessment will be done; vitals will be noted, questionnaire will be filled-in and blood will be collected for various parameters.

Study Conduct:

Patients screened, eligible and willing will be enrolled in the study and IP will be dispensed. During screening, inclusion-exclusion criteria will be applied. Those fulfilling the criteria will be given detailed information about the study. Of those who are willing to participate will be asked to sign the informed consent form. Study coordinator with the principal or co-principal investigator will participate in the consent process.

Day of consenting will be done on the day of screening. After signing the consent form, on enrollment day, physical examinations will be done; blood will be withdrawn for investigations, case record form will be filled and IP will be dispensed. A copy of duly signed informed consent form will be given to them.

Follow-up Visit 1 [5^th^ day (+ 1) of the day of enrollment]: Questions will be asked about adherence, missed doses if any and adverse events if any. NP swab will be collected for RT-PCR of COVID-19

Follow-up Visit 2 [15^th^ day (+ 2) of the day of enrollment]: All the procedures for this visit will be the same as that of Visit 1, except that swab will not be collected for RT PCR.

Follow-up Visit 3 [30^th^ day (+ 2) of the day of enrollment]: All the procedures for this visit will be the same as that of Visit 2, and in addition, blood will be drawn for various markers.

Discontinued Patients:

Patients will be withdrawn/dropped from the study if they violate the protocol e.g. by participating in other study, by not taking the IP, not coming to the hospital for follow-up etc. Patients developing any serious disease, patients wanting to withdraw will also be withdrawn from the study.

Patients who have not turned for clinical follow-up will be called telephonically up to three times after the window period is over. During consenting they will be asked if it is alright with them.

However, as it is a ‘intent-to-treat’ (ITT) study design, data collected of such patients, till they are dropped out/withdrawn from the study will be included in the analysis.

Patients will be insisted to visit during the window-period. Those who miss this will still be continued into the study. On case-to-case basis, protocol waivers will be granted by the co-PI and/or the PI.

Protocol violations will be notified to the EC and to the concerned person responsible for such violations. Appropriate training will be given by the sponsor or by Quest clinical services. Quest clinical services have rights to change the person and notify the EC accordingly.

In case of continuous or repetitive violations hampering the study design in total or jeopardizing the safety of patients, study will be terminated after informing the EC.

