# Data Analysis

Overall blinding will be broken at 30 days i.e.at the end of the study. Depending upon ADRs / SAEs, individual blinding might be broken on case-to-case basis.

Paired t test and any other appropriate test will be applied for analysis.

As this is intent-to-treat design, all the data, even the dropped-out patients’ and lost to follow-up patient’s collected data will be analyzed.

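### Withdrawal from the study for stopping the capsules, not attending or serious disease ends outcome collection, which the intent-to-treat label does not cover

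*Protocol*

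**What the plan says.** The Discontinued Patients text of the Protocol (Study Assessments) lists the grounds for withdrawal from the study. Protocol violation is one, with examples that include "by not taking the IP, not coming to the hospital for follow-up etc". Illness and patient choice are the others: "Patients developing any serious disease, patients wanting to withdraw will also be withdrawn from the study".

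The same text then calls the design intent-to-treat, because "data collected of such patients, till they are dropped out/withdrawn from the study will be included in the analysis". Data Analysis repeats the idea. It opens with "As this is intent-to-treat design, all the data" and goes on to say that, along with the dropped-out patients' data, "lost to follow-up patient’s collected data will be analyzed".

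The only contact described for patients who do not turn up is that they "will be called telephonically up to three times after the window period is over". No outcome assessment is attached to those calls. About patients who miss the visit window, the text says: "Those who miss this will still be continued into the study".

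**The concern.** Intent-to-treat needs every randomised patient to be followed for the outcome and analysed in the assigned arm, whether or not treatment continued. Here the protocol itself ends follow-up after events that occur after randomisation and that treatment can influence: stopping the capsules, failing to attend, and serious illness. The inclusion criteria admit mild to moderate COVID-19, so serious disease can be read to include worsening of the disease under study. That overlaps with the primary outcome, which includes early recovery, and with the secondary outcome on sequelae.

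If these events differ between arms, the patients with later data are no longer the randomised groups. A statistical analysis plan can say how missing values are handled, but it cannot recover outcomes that the protocol stopped collecting.

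**Working it through.** **1. What is lost, by time of withdrawal** (Study Design, the outcome list, and the Study Assessment Table)

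| Outcome | Scheduled | Withdrawn before day 5 | Withdrawn between day 5 and day 30 |
| --- | --- | --- | --- |
| Viral load | day 0, day 5 (day 3 in 5 per arm) | day-5 value lost | kept |
| Immune markers, IgG, IgM | day 0, day 30 | day-30 value lost | day-30 value lost |
| Liver and kidney function | day 0, day 30 | no post-baseline value | no post-baseline value |
| Recovery and sequelae | through follow-up | later status lost | later status lost |
| Adverse events | every visit | later events lost | later events lost |

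So the day-5 viral load is only partly exposed, while the day-30 outcomes and the laboratory safety tests are fully exposed.

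**2. The plan's own figure.** Inputs from the sample size table: 5% versus 35%, two-sided 5% level, 80% power, ratio 1:1. The mean proportion is (0.05 + 0.35)/2 = 0.20.
- Fleiss, without continuity correction: [1.960·√(2·0.20·0.80) + 0.842·√(0.05·0.95 + 0.35·0.65)]² / 0.30² = 26.7, so 27 per arm (54 in total).
- Kelsey: (1.960 + 0.842)²·0.20·0.80·2 / 0.30² = 27.9, so 28 per arm (56 in total).

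Both match the table. The sample size is not the fault here.

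**3. Possible bias (assumed values).** The protocol gives no withdrawal rates. Let r be the true recovery rate, the same in both arms, and w the share withdrawn in an arm. Suppose all withdrawn patients are non-recovered and are left out of the denominator. The observed rate is then r/(1 − w). The value r = 35% is only a convenient level taken from the sample size table.

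| Withdrawn, arm A vs arm B | Observed A | Observed B | False difference |
| --- | --- | --- | --- |
| 10% vs 10% | 0.35/0.90 = 38.9% | 38.9% | 0 |
| 10% vs 20% | 38.9% | 0.35/0.80 = 43.8% | 4.9 points |
| 0% vs 20% | 35.0% | 43.8% | 8.8 points |
| 10% vs 30% | 38.9% | 0.35/0.70 = 50.0% | 11.1 points |

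The arm that loses more patients looks better. For 10% versus 20%, the false difference is 2.8 points at r = 20% and 6.9 points at r = 50%. If withdrawn patients stay in the denominator as not recovered, both arms show 35% and the difference is zero.

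**4. Precision.** At 30 per arm and 5% versus 35%, power is 84.6% with no loss, 80.5% with 10% lost, 75.4% with 20% and 69.4% with 30%. Before the number evaluable falls below 56, a total of 60 can lose 1 − 56/60 = 6.7% and a total of 75 can lose 1 − 56/75 = 25.3%.

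**5. Passages that do not fit together**
- Study Assessments withdraws patients for not coming to hospital, but continues those who miss the window. Study Design also makes follow-up 2 clinical or telephonic and follow-up 3 telephonic with blood taken off site, so absence from hospital is not a clear trigger after follow-up 1.
- Methods and Procedures, and Study Treatment (c), allow the product to be stopped for safety without saying that the patient leaves the study. Study Assessments makes not taking the product a ground for withdrawal. Study Treatment (e) discontinues from the study a patient for whom remaining could be harmful.

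**The case against.** Several points on the other side stand.

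- **Data before withdrawal are kept.** A reader might infer that the rule deletes the worst outcomes. The documents do not say so. The serious disease that triggers withdrawal is known at that time, and nothing forbids counting that patient as not recovered.
- **Denominators are not stated.** One could build an example in which every worsening patient disappears, both arms show full recovery, and a real harm vanishes. That requires withdrawn patients to be removed from the denominator, which no section says. The table in step 3 makes the same assumption and must be read with it.
- **Day 5 is less exposed than it looks.** Adherence is first asked about at the visit where the swab is taken. A material shift in day-5 viral load would need patients who worsen to be withdrawn before that swab.
- **Harm would not be invisible.** Adverse events are recorded at every visit, and serious ones go to the ethics committee within 24 hours. What is truncated is later events and the day-30 liver and kidney tests.
- **Serious disease is ambiguous.** It may mean a new intercurrent illness rather than worsening COVID-19.
- **The paired t test is not the only option.** Data Analysis also allows any other appropriate test, although no test can use an outcome that was not collected.
- **The visit rules may be reconcilable** if late and never attending are different things. The text does not draw that line.
- **The trial is exploratory**, and with 75 enrolled it can absorb about a quarter lost.

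These points limit the size of the problem. They do not supply the missing outcomes or make the analysis intent-to-treat.

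**Conclusion.** The concern holds in a limited form. The protocol ends outcome collection for reasons that can depend on treatment and outcome, and analysing only what was collected until then does not earn the intent-to-treat label. The main losses are the day-30 immune markers, the only scheduled post-baseline liver and kidney tests, and later recovery and sequelae; the day-5 viral load is lost only for patients withdrawn earlier.

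The direction and size of any bias cannot be derived from the documents. Under the step 3 assumptions, unequal withdrawal gives a false difference of roughly 5 to 11 points, and equal withdrawal gives none. It is too strong to say that the worst outcomes are dropped by rule, or that harm would go unseen. The point still merits an amendment, because outcomes not collected cannot be restored at the analysis stage.

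**What to change.** Amend Study Assessments and Data Analysis so that stopping study medication and leaving the study are separate events. Suggested content:

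- Patients who stop study medication, deviate from the protocol, miss a visit or develop serious disease stay in follow-up for the scheduled day-5, day-15 and day-30 assessments, by telephone where that is already allowed, unless they withdraw consent.
- Progression or death is recorded as an outcome and counted as not recovered. State whether serious disease includes worsening COVID-19.
- All randomised patients are analysed in their assigned arm.
- Visits outside the window are recorded with the actual day, and the sentences on non-attendance and on missing the window are reconciled.

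Leave the investigator's freedom to stop treatment unchanged. Reconcile the withdrawal text with Methods and Procedures and with Study Treatment (c) and (e), so that stopping for safety does not by itself end outcome collection.

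The cost is the amendment wording and some extra effort to follow patients who have stopped the capsules. The telephone contacts and blood draws are already scheduled, and the sample size calculation does not change.

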# Randomization Process:

An alphanumeric coded set of IP/Placebo containers will be used. Participants will be automatically randomized to two groups in the ratio 1:1. Blind will be broken after the last follow-up of last enrolled subject is over.

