# Study Design

Overview of the Study Design

- This is a randomized, 2-arm, parallel group, double-blind, 1:1 ratio, controlled, exploratory trial with a study period of 30 days from the of enrolment.
- A total of up-to 75 known COVID-19 positive (with positive RT-PCR) patients will be enrolled in the study.
- All the patients enrolled in the study will get the Investigational Product (IP-1 and IP-2), or 2 capsule of Placebo in similar sized and colored bottles, two times daily for the 1^st^ 15 days. From 16^th^ day onwards patients will get one capsule twice daily i.e. IP-2 or capsule placebo up to day 30.
- Patients will undergo laboratory investigations upon enrolment and on last visit. RTPCR for COVID will be done on day 5 (+ 1 day).
- Patients and doctors treating will not be knowing what the participating subject has received. Subjects will be given coded bottles, containing dose for 30 days.
- No medicine which his/her physician is giving will be stopped. No modifications shall be suggested in their diet and daily routine physical activities.
- Thus, patients enrolled in the study will get the IP / Placebo in addition to the standard of care which they were already receiving at the time of enrolment.
- Half of patients will be getting Cap. IP and half will be getting Cap. Placebo throughout the study duration of 1 month.

Study period for enrolled patients will be 30 days:

- Enrollment (day 0): After Informed Consent Process, Demographics and other information for CRF will be recorded. Investigations: COVID 19 RTPCR, Lymphocyte subset analysis (TH1, TH2, Th17, IL6, NK Cells and CD markers); Immunoglobulin IGG (Serum); Immunoglobulin IGM (Serum); Liver Function Test and Kidney Function Test will be done. Cap. bottle will be given to the patients with the dose lasting for 30 days.
- Day 3±1: COVID-19 RT PCR (quantitative) test will also be conducted on day 3 (±1) on 5 subjects of each group
- Follow-up 1: Day (5±1): COVID-19 RT PCR (quantitative) test will be conducted for all subjects on Day (5±1). CRF will be filled for knowing the overall status.
- Follow up 2 (15^th^ day+ 2 days): This follow up will be clinical/telephonic. CRF will be filled for knowing the overall status.

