**Sample size: Cross- sectional, Cohort and Randomized Clinical Trials**

| Two sided significance level ( 1 alpha) | 95 |
| --- | --- |
| Power ( 1-beta. % chance of detecting) | 80 |
| Ratio of sample size, Unexposed/ exposed | 1 |
| % of Unexposed with outcome | 5 |
| % of Exposed with outcome | 35 |
| Odds ratio | 10 |
| Risk/ Prevalence ratio | 7 |
| Risk/ Prevalence | 30 |

|  | Kelsey | Fleiss |
| --- | --- | --- |
| Sample Size Exposed | 28 | 27 |
| Sample Size Non exposed | 28 | 27 |
| **Total Sample Size** | **56** | **54** |

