# Subject Eligibility:

(a) Inclusion Criteria

1. Age > 18 years
2. All sexes
3. Case definitions for inclusion in the study will include mild to moderately severe cases as defined in the Guidance on appropriate treatment of suspect/confirmed case of COVI19 issued by Ministry of Health and Family Welfare, Govt of India on 07 Apr 2020.
   Mild: Cases presenting with fever and/or upper respiratory tract illness (Influenza like Illness, ILI); Moderate: Pneumonia with no signs of severe disease (Respiratory Rate 15 to 30/minute, SpO2 90%-94%). OR
4. Laboratory confirmed SARS CoV-2 infection within last 10 days or SARS CoV-2 test result pending with a high clinical suspicion as defined by: Cough of more than 10 days duration OR
5. Bilateral pulmonary infiltrates on chest X Ray / CT scan or new hypoxaemia defined as SpO2 <94% on room air, where no alternative explanation for respiratory symptoms can be given

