# Study Treatment:

(a) Dosing schedule (dose, frequency, and duration):

Participants will be dispensed IP, which is Cap IP or Cap. Placebo.

Dose of the IP is: For 15 days two Capsules two times a day, and from 16^th^ day one capsule two times a day upto day 30. It is to be administered orally with plain water.

IP, in any dose, needs to be taken for a period of 30 days in total; from the day of enrollment.

IP will be given from the study site by the study coordinator, free of cost. All other concomitant medicines prescribed by the treating physician/doctor has to be taken by the patient.

Half of the patients enrolled will get Placebo (inert substance) in the capsule throughout the study period. However, neither patient nor the investigators will know, who is receiving what.

(b) Study drug supplies and administration: Study medication will be provided by AMAI Charitable Trust, Pune, which is the sponsor of the trial. Quest clinical services will distribute the same to the enrolled patients in the manner mentioned in this protocol. Investigational drug formulation has been manufactured following all the GMP regulations.

The IP will be securely stored in cupboards; at room temperature. Expiry date will be verified before giving the IP to the patients. CRC will document the code on the bottle to given to corresponding patient.

(c) Dose modification for study drug: In case of any serious adverse event, that warrants to break the blind, sponsor will be contacted. Dose might be modified or IP might be stopped, in the best safety interest of the patient.

(d) Possible drug interactions: As this is an herbo-mineral compound, involving safe profile herbs, no drug interactions are expected. Investigator already has an experience with the combination. When he has used it for other infectious and non-infectious disorders for immunity boosting.

(e) Concomitant therapy: As a part of the study design, all the medicines that the patient is supposed to take for his/her other condition(s), patient might be having, will be allowed. There is no drug that is not allowed, provided, it is prescribed by the treating physician. If the PI or co-PI decides that by remaining in the study could be harmful for his/her health, patient will be discontinued from the study.

(f) Blinding procedures:

Placebo is used in this study, to allow blinding of investigators and subjects to treatment and minimize bias in the evaluation of safety and efficacy assessments,

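### Minor, cheap improvement: mild cases and pneumonia are randomised from one 1:1 pool without balancing on severity, which leaves the estimate open to avoidable chance imbalance

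*Protocol*

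**What the plan says.** The Study Design section describes the trial thus: "This is a randomized, 2-arm, parallel group, double-blind, 1:1 ratio, controlled, exploratory trial". The Randomization Process section adds only that the containers carry alphanumeric codes and that "Participants will be automatically randomized to two groups in the ratio 1:1". No section mentions strata, blocks or minimisation. On dispensing, Study Treatment (b) says "CRC will document the code on the bottle to given to corresponding patient", and nothing states the order in which bottles are used.

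Inclusion item 3 under Subject Eligibility takes two kinds of patient: "Mild: Cases presenting with fever and/or upper respiratory tract illness (Influenza like Illness, ILI" and "Moderate: Pneumonia with no signs of severe disease (Respiratory Rate 15 to 30/minute, SpO2 90%-94%). OR". Item 5, joined by OR, also admits bilateral infiltrates or "new hypoxaemia defined as SpO2 <94% on room air", with no lower saturation limit. Exclusion item 2 allows up to seven days of symptoms.

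The primary outcome is decline in viral load at 5 days together with early recovery. IL-6, T-cell and NK markers at day 30 are secondary. Data Analysis names a paired t test and leaves room for other suitable tests. It neither sets nor rules out adjustment for severity.

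The size is given as 30 per arm (flow chart), 60 extendable to 150 (Methods and Procedures), and more than 60 up to 75 (sample-size text).

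**The concern.** In a trial this small, 1:1 allocation from one pool can leave noticeably more pneumonia patients in one arm. If severity affects outcome, the observed difference then carries a case-mix component that a reader of the baseline table cannot separate from treatment.

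The protocol itself supports a link for some outcomes. Its pathophysiology section says IL-6 rises with severity, and IL-6 is a secondary outcome. Early recovery plausibly depends on how ill the patient is at entry. For day-5 viral load no such link is stated, so there it is an assumption.

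At stake are the precision and credibility of the estimate. Stratified allocation has to be built into the bottle coding before enrolment; no later analysis plan can add it.

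**Working it through.** **1. The plan's own figure.** Inputs from the sample-size table: 5% vs 35%, two-sided 5%, 80% power, 1:1.
- Fleiss: [1.960√(2×0.20×0.80) + 0.842√(0.05×0.95 + 0.35×0.65)]² / 0.30² = (1.109 + 0.441)² / 0.09 = 26.7, so 27 per arm.
- Kelsey: (1.960 + 0.842)² × 2×0.20×0.80 / 0.30² = 27.9, so 28 per arm.

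Both match the protocol.

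**2. How often severity is unbalanced.** With M moderate patients among N, the number k in one arm is Hypergeometric(N, M, n₁). The imbalance is |k/n₁ − (M−k)/n₂|. The moderate share is not in the documents; I take 20-50%.

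| Arms | Moderate patients | P(imbalance ≥ 20 points) |
|---|---|---|
| 30/30 | 12 of 60 | 10.4% |
| 30/30 | 13 of 60 | 5.7% |
| 30/30 | 15 of 60 | 7.2% |
| 30/30 | 20 of 60 | 17.0% |
| 30/30 | 30 of 60 | 19.6% |
| 37/38 | 15 of 75 | 1.9% |
| 37/38 | 30 of 75 | 10.0% |
| 37/38 | 36 of 75 | 10.7% |
| 37/38 | 37 of 75 | 6.6% |

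The figures jump because counts are whole. At 30/30 an odd M needs a difference of 7 patients to reach 20 points; an even M needs 6. Over every M from 20% to 50%, the range is about 6-20% at 30/30 and 2-11% at 37/38.

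**3. How far the estimate moves.** Shift = imbalance × outcome gap between severities.
- Continuous outcome, assumed gap 0.5-1.0 SD: 0.20 × 0.5 = 0.10 SD to 0.20 × 1.0 = 0.20 SD. The difference detectable at 30 per arm is (1.960 + 0.842) × √(2/30) = 0.72 SD.
- Binary outcome, assumed gap 30 points: 0.20 × 30 = 6 points, against a planned difference of 30 points.

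**4. Error rates (simulation, 30 per arm).**
- Binary null, 30-point severity gap: overall type I error 4.7-4.9%; given an imbalance of 20 points or more, 7.2-8.4%.
- Continuous null, gap 0.5-1.0 SD: about 6-8% at a 20-point imbalance and 7-13% at 27 points.
- 5% vs 35%: power about 88% overall; 76-84% when the active arm has at least 20 points more moderate cases; 92-96% when it has at least 20 points fewer.

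**5. What the remedy buys.** With severity split evenly and an unadjusted test, power is 88-89% and type I error 3.4-3.9%, so stratifying alone mainly removes the bad draws. For adjustment, with moderate share f and gap d in within-severity SDs, R² = f(1−f)d² / [1 + f(1−f)d²]. The equivalent gain in patients is 1/(1−R²) − 1 = f(1−f)d². At f = 0.20, d = 0.5 this is 0.20×0.80×0.25 = 4%; at f = 0.25, d = 0.5 it is 4.7%; at f = 0.50, d = 1.0 it is 25%.

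**The case against.** The strongest reply is that nothing here is wrong. Unstratified 1:1 randomisation is a valid design, the trial is labelled exploratory, and the ordinary test already allows for chance imbalance. This stands: there is no systematic bias and no contradiction.

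Covariate adjustment is commonly left to a statistical analysis plan, which is not at hand. RT-PCR at day 0 and day 5 also permits a baseline-adjusted viral-load analysis. This stands too, so the protocol's silence on covariates is not held against it. It does not answer the allocation point, which must be settled when the bottles are coded.

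A reader might infer that imbalance could create or hide a day-5 effect. The documents do not support that. Even with a large assumed severity gap, a 20-point imbalance moves the difference by 6 of the planned 30 points. Power stays at 76-84% in the unfavourable case, and no passage ties mild versus moderate disease to viral decline. A reader might also infer that precision is being discarded, or that adjustment is worth more than a quarter again in patients. The first cannot be known without the analysis plan. The second would need prognostic strength beyond the severity gap assumed here.

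The unstated dispensing order might suggest a concealment failure. The protocol keeps the code list with the sponsor, away from site and CRO, so that does not follow either.

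**Conclusion.** The point holds as a minor, inexpensive improvement. The protocol pools two recognisable severity groups, knows the group at screening and does not use it in allocation. The result is an avoidable chance of a poorly balanced comparison: about 6-20% at 30 per arm for an imbalance of 20 points or more, falling to about 2-11% at 37/38. The likely damage is a shift of 0.10-0.20 SD and a conditional false-positive rate of about 6-8% in place of 5%, with the unconditional rate unaffected.

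These sizes rest on an assumed moderate share of 20-50% and an assumed severity gap of 0.5-1.0 SD; neither is in the documents. For effects smaller than the very large planned one, the same shift would matter proportionately more.

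**What to change.** In Randomization Process, state that:
- the sponsor prepares two coded container series, by severity at screening, from a computer-generated 1:1 list in permuted blocks whose sizes are not told to the site;
- the site dispenses the next number in the patient's series;
- patients entering by inclusion items 4 or 5 go to a named series, since those routes carry no severity label.

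The stratum needs one definition. Inclusion item 3 calls saturation of 90-94% moderate, while the classification table in the symptomatology section calls pneumonia with saturation below 92% severe. The two passages must be reconciled.

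In Data Analysis, or in the analysis plan, include the severity stratum and days since symptom onset as covariates in the between-arm comparison. Under the assumed gap, adjusting for severity is worth roughly 4-25% more patients. Without adjustment, stratifying makes the test slightly conservative.

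Cost: a second bottle series and some spare bottles. The ten sub-study codes (five per arm) in Study Design must be drawn across both series. No extra visits or patients are needed, and the sample size is unchanged.
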